# Preoperative supine time for adrenal venous sampling: a prospective randomized controlled trial

**DOI:** 10.1186/s13063-023-07872-2

**Published:** 2024-01-02

**Keywords:** Primary aldosteronism, Adrenal venous sampling, Supine time

## Abstract

**Background:**

Primary aldosteronism (P.A.) is the most common form of secondary hypertension, accounting for 5% of hypertensive patients and 17–23% of patients with resistant hypertension. Compared to primary hypertension, P.A. is more prone to cause severe organ damage and even early death. Adrenal venous sampling (AVS) is a practical confirmatory test for subtyping aldosterone-producing adenoma and bilateral adrenal hyperplasia, helping physicians to make an accurate decision between surgery or medication. According to guidelines, supine in bed before AVS is recommended for a desirable result of AVS. However, investigations about the most optimal preoperative supine time before AVS are lacking.

**Methods/design:**

This is a multi-center prospective randomized controlled study. One hundred twenty patients diagnosed as P.A. and willing for AVS examination will be included. Participants will be randomly allocated to a 15-min supine time group or 2-h supine time group. The primary outcome is the degree of biochemical remission (serum potassium and orthostatic ARR). The secondary outcomes are degrees of clinical remission (blood pressure, type and dose of antihypertensive drugs), the technical success rate, and the adverse event of AVS (selective index ≥ 2 is considered successful surgery without corticotropin stimulation).

**Discussion:**

P.A. is an intractable public health problem, and many techniques including AVS have been developed to identify this disease correctly. This study will help to understand whether the length of preoperative supine time would affect the diagnostic efficacy of AVS and thus help to formulate a more reasonable AVS procedure.

**Trial registration:**

ClinicalTrials.gov NCT05658705. Registered on 10 September 2022.

**Supplementary Information:**

The online version contains supplementary material available at 10.1186/s13063-023-07872-2.

## Introduction

### Background

Primary aldosteronism (P.A.) is a disease caused by excessive autonomous aldosterone from adrenal tumor or hyperplasia, characterized by the inhibition of the renin-angiotensin system, sodium retention, and excessive excretion of potassium and hydrogen [1]. P.A. was regarded as a rare disease since it was first discovered by Conn in 1955 [2] for it was found only in less than 1% of hypertensive patients [3]. However, recent studies have noticed that P.A. accounts for 5% of hypertensive patients in primary care [4], and the prevalence in patients with resistant hypertension has reached 17–23% [5]. A study on the Chinese population with newly detected hypertension also profiled at least 4% of patients suffered P.A [6]. Besides, P.A. is a significant cause of increased stroke risk, coronary artery disease, atrial fibrillation, ventricular hypertrophy, and renal damage [7]. It could be assumed that most P.A. patients missed proper diagnosis and suffered cardiovascular damage, which may explain the limitation of traditional hypertensive drugs on resistant hypertension.

P.A. includes two main subtypes: aldosterone-producing adenoma (APA, accounting for about 35%) and bilateral adrenal hyperplasia (BAH, accounting for about 60%). Other rare subtypes include primary adrenal hyperplasia, family aldosteronism, and aldosterone-secreting adrenocortical carcinoma [1, 8]. It is controversial whether P.A. patients should be treated with surgery or drugs [9]. Unilateral adrenalectomy is suggested for most patients with adenoma or primary adrenal hyperplasia, which statistically satisfied the goal of clinical and laboratory remission [10, 11]. However, anti-RAAS drugs and glucocorticoids are more recommended for BAH or family aldosteronism patients [12].

Raising the accuracy of diagnosis and subtyping is extremely important for P.A. patients. Screening of P.A. is based on the aldosterone to renin ratio (ARR), and people with abnormally elevated ARR should be screened by further oral salt loading or captopril confirmatory tests [13]. P.A. subtyping test is also an essential, although difficult and challenging, step [13]. Adrenal venous sampling (AVS) was now regarded as the gold standard for P.A. subtyping but only performed in limited centers [12, 14]. Our team was experienced in this technique. Recently, we have developed a computed tomography image fusion, coaxial guidewire technique, and fast intraprocedural cortisol testing (CCF) technique, which significantly increased the success rate of AVS to 98% and shortened the whole procedure time [15]. Moreover, we are still committed to exploring a more optimized AVS procedure.

AVS outcome was interpreted by comparing aldosterone levels in the adrenal venal of the dominant and nondominant side, which could be affected by the position change [16]. Before AVS without corticotropin injection, patients were suggested to keep a supine position to avoid aldosterone fluctuation [13, 17]. However, the length of supine time before AVS had no established standard, although authoritative guidelines recommend recumbency times ranging from 1 h to overnight [13, 17]. In previous work, we chose 1–2 h of supine time as the guideline suggested [17]. We observed many problems were caused by excessive supine time, such as patient’s urinary retention and anxiety, while reduced supine time was found to be more friendly for these patients.

The cortisol level of patients is also an important factor affecting the selective index (S.I.) during AVS. A cohort study showed that at least 15 min of rest before blood sampling was enough to minimize the stress effect and guarantee a satisfactory outcome [18]. Thus, we speculate that 15-min supine time is enough to minimize the fluctuation of aldosterone and cortisol fluctuation caused by position change and preoperative stress.

However, evidence of the most optimal supine time before AVS still lacks, which could simultaneously improve patient satisfaction and compromise the success rate. We expect that the shortened supine time will improve patient experience and ensure the success rate at the same time.

### Objectives

The primary aim of this study is to compare the effects of preoperative 15-min or 2-h supine to the efficacy of AVS

### Trial design

The study was designed as a multi-center, prospective, two-arm, parallel-group, randomized controlled trial. The protocol is reported in line with the Standard Protocol Items: Recommendations for Interventional Trials (SPIRIT) guidelines following the SPIRIT schedule (Fig. 1) and trial flow chart (Fig. 2). The study was registered on ClinicalTrials.gov: 05658705. The fundamental hypothesis is that reduced preoperative supine time did not affect the subtyping efficacy of AVS. Our hypothesis is based on a simple premise: 15-min preoperative supine time is enough to minimize the fluctuation of serum aldosterone and cortisol levels, thus maintaining the accuracy of AVS outcome.

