#### Primary outcome

Rate of biochemical remission

Biochemical outcome evaluation in 3 and 6 months after AVS: serum potassium, orthostatic ARR. All these data will be recorded in the PASO table [11] (feasible criteria for the classification of outcomes of adrenalectomy for the treatment of unilateral primary aldosteronism). The detailed criteria of complete, partial, and absent biochemical remission are shown in Fig. 3.

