### Statistical analysis

An independent statistician will complete the statistical analysis of the study result via the SPSS V25.0. Baseline characteristics will be described by descriptive statistics. *x̅* ± *s* will represent continuous variables with the normal distribution, and the *t* test will compare the differences between the two groups. The Mann–Whitney *U* test will be used in continuous variables that were not normally distributed. Categorical variables will be expressed as frequency (%), and the chi-square test will be used to compare the differences between the two groups. Effect estimates will be provided with corresponding 95% confidence intervals, and *P* values ≤ 0.05 will be considered statistically significant. All randomized participants will be included in the analyses, and data will be analyzed in the group where the participants were randomized initially. The experimental group includes the available data from the 15-min supine group, and the control group includes the available data from the 2-h supine group. The principles of intention-to-treat analysis will be used to preserve the unique benefit of randomization, regardless of whether that participant received the allocated intervention. Multiple imputation (MI) using the mice package in R will be applied to analyze the missing data.

Further secondary analyses will include pre-specified subgroup analyses according to age and the two stratification/minimization variables, investigated by introducing the relevant interaction with treatment allocation into the regression model. In addition, to assess the stability of any intervention effect, we will fit a mixed model for the primary outcome at 3 and 6 months, adjusted for baseline measures.

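### The hypothesis is that 15 minutes supine does not affect AVS efficacy, but the trial is sized and tested for a difference and no non-inferiority margin is stated

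*Protocol article*

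**What the plan says.** **Hypothesis.** Trial design: "The fundamental hypothesis is that reduced preoperative supine time did not affect the subtyping efficacy of AVS". The premise follows at once: "15-min preoperative supine time is enough to minimize the fluctuation of serum aldosterone and cortisol levels, thus maintaining the accuracy of AVS outcome". The Background section points the same way: "We expect that the shortened supine time will improve patient experience and ensure the success rate at the same time". That sentence concerns the success rate, and successful catheterization is a secondary outcome, so it shows the intent of the trial and not a decision rule.

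**Objective.** The Objectives section is neutral: "The primary aim of this study is to compare the effects of preoperative 15-min or 2-h supine to the efficacy of AVS". It names no superiority, non-inferiority or equivalence framework.

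**Primary outcome.** The rate of biochemical remission, classed as complete, partial or absent: "Biochemical outcome evaluation in 3 and 6 months after AVS: serum potassium, orthostatic ARR".

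**Sample size.** 60 per group to detect an effect size of 0.5 with a 5% type I error and 90% power; 120 patients in total, with a 20% loss to follow-up allowed for.

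**Analysis.** For categorical variables "the chi-square test will be used to compare the differences between the two groups", and P "values ≤ 0.05 will be considered statistically significant". The same section adds: "Effect estimates will be provided with corresponding 95% confidence intervals". No margin, and no rule for reading an interval against a limit, appears anywhere in the document.

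**The concern.** The claim to be supported is that efficacy is kept when supine time is cut. A test for a difference works the other way. Rejection would contradict the hypothesis, and failure to reject is the only outcome that could favour it. Failure to reject becomes more likely with fewer patients, more dropout and noisier measurement, so the weaker the trial, the easier the hypothesis is to support.

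The Background section says that guidelines recommend 1 h to overnight, and AVS results steer patients towards adrenalectomy or medication. A non-significant result could be cited for 15 minutes while the data remained compatible with a material loss of remission. The type of hypothesis and its margin also determine the sample size, so this is not a detail that can wait for an analysis plan.

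**Working it through.** **1. The plan's own figure.** Inputs from the Sample size section: effect size 0.5, α = 0.05, power 90%. The scale and the sidedness are not stated. Read as a standardised mean difference, two-sided:

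n per arm = 2(1.960 + 1.282)² / 0.5² = 84.06, so 85.

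This does not give 60. At 60 per arm the power for that difference is 78%, and at 48 per arm it is 69%. The mismatch is a separate matter, and the present point does not depend on it. What matters here is that 0.5 is a difference to be detected and not a margin to be excluded.

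**2. Numbers per arm.** The section gives 60 per group as the calculated need and also as the number after allowing for 20% loss. I therefore use both 60 and 60 × 0.80 = 48. Multiple imputation is planned, but it does not restore the information lost with 20% of outcomes.

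**3. Chance that a real loss is non-significant.** Remission rates are my assumptions, since the document gives none. With control rate p₁, 15-min rate p₂ and their mean p̄:

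power = Φ{[(p₁ − p₂) − 1.96·SE₀] / SE₁}, where SE₀ = √[2p̄(1 − p̄)/n] and SE₁ = √{[p₁(1 − p₁) + p₂(1 − p₂)]/n}.

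Example, 80% to 70% at n = 60: SE₀ = 0.0791, SE₁ = 0.0785, argument = −0.700, power 24%, non-significant 76%.

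| True rates (2 h → 15 min) | Non-significant, 60 per arm | Non-significant, 48 per arm |
|---|---|---|
| 60% → 50% | 81% | 84% |
| 80% → 70% | 76% | 80% |
| 90% → 80% | 67% | 72% |
| 80% → 65% | 55% | 62.5% |
| 90% → 75% | 42% | 51% |
| 95% → 80% | 30% | 39% |
| 80% → 60% | 33% | 43% |

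**4. What the planned interval can exclude.** With equal true rates p, SE = √[2p(1 − p)/n]. The 95% half-width is 1.96·SE. The smallest margin with 90% power (one-sided 0.025, the lower limit of a two-sided 95% interval) is (1.960 + 1.282)·SE.

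| Remission (assumed) | Half-width, 60 / 48 per arm | Margin at 90% power, 60 / 48 per arm |
|---|---|---|
| 90% | 11 / 12 points | 18 / 20 points |
| 80% | 14 / 16 points | 24 / 26 points |
| 50% | 18 / 20 points | 30 / 33 points |

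**5. A narrower margin.** For a 10-point margin with equal true rates, power = Φ(0.10/SE − 1.96). At 80% remission it is 28% (60 per arm) or 23% (48 per arm). At 90% remission it is 45% or 37%. Reaching 90% power would take 337 evaluable patients per arm at 80% remission, or 190 at 90%.

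**The case against.** **The aims can be read as neutral.** Objectives only speaks of comparing, the Discussion does the same, and a difference test fits that. The Trial design sentence might be no more than the authors' expectation. This stands in part. But the sentence is called the fundamental hypothesis, and the plan gives no rule by which it could be supported.

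**Intervals are planned.** This stands. The analysis already yields the quantity needed; the margin and the decision rule are what is missing.

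**Stronger readings that the text does not bear out.**
- A reader might infer that the investigators plan to report a non-significant result as proof of equal efficacy. No section says so. It is only the sole route the written rule leaves open.
- A reader might infer that an important loss would most likely be missed. That depends on the loss and the control rate: in the first table, the last two rows fall well below one half. The document does not define an important loss.
- A reader might infer that the trial cannot support its claim at all. With 90% remission and a 20-point margin, or 95% and 15 points, 48 evaluable patients per arm would be enough, provided that the margin is declared beforehand.
- A reader might fault intention-to-treat as the only analysis set. A per-protocol set is commonly left to the analysis plan, which is not at hand, and nothing in the document suggests much crossover for a single rest period before the procedure.

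**Conclusion.** The point holds in this form: a no-effect hypothesis is paired with a sample size for detecting an effect, a difference test at P ≤ 0.05 and no margin. Under the written rule only non-significance could support the hypothesis, and with 48–60 patients per arm non-significance is the more probable result for a true 10-point loss at each control rate tried (67–84% for 60% to 90%). For a 15-point loss from 80% it is 55–62.5%; for larger losses, or 15 points from a high control rate, it is often less than half. All of these figures rest on assumed remission rates, equal arms and normal approximations. The mismatch itself rests on no assumption and can be read from the text. It should be settled before results are known, because the primary conclusion depends on it.

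**What to change.** 1. Restate the primary hypothesis as non-inferiority of 15 min to 2 h on the risk difference in biochemical remission, with one named definition of remission (complete, or complete plus partial) and one named time point (3 or 6 months).
2. Fix a clinically justified margin before results are known.
3. Conclude non-inferiority only if the lower limit of the planned two-sided 95% confidence interval for the difference (15 min minus 2 h) lies above minus that margin. State that P > 0.05 will not be read as no effect.
4. State the margin that 120 patients can support at the protocol's own 90% power (about 18–30 points at 60 per arm, 20–33 points at 48 per arm, for remission of 90% down to 50%) and limit the conclusion to it. If the justified margin is narrower, recompute the sample size.

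A per-protocol sensitivity analysis would be a sensible option but is not essential to this point.

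Cost: rewording of the hypothesis, sample-size and analysis sections; no new data. The downside is that the permitted conclusion becomes less favourable if the supportable margin is wide, and more patients would be needed if a narrower one is required.

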**Fig. 1 Fig1:**
[figure not shown]
Standard Protocol Items: Recommendations for Interventional Trials (SPIRIT) enrollment schedule, interventions, and assessments

**Fig. 2 Fig2:**
[figure not shown]
Flow chart of the trial

## Methods

### Study setting

This study is taking place in three centers in China: The Second Affiliated Hospital of Zhejiang University of Medicine (initiation center), the First People’s Hospital of Jiashan (participating center), and the First People’s Hospital of Yuhang District of Hangzhou (participating center).

### Eligible participant

Participants are the patients considered P.A. and with willingness for AVS. Screening and preliminary classification of P.A. patients will be completed by endocrinology doctors, who will also be responsible for follow-up and medication adjustment. AVS and unilateral adrenalectomy will be carried out by a doctor of vascular surgery and urology.

The study was approved by the Ethics Committee of the Second Affiliated Hospital of Zhejiang University School of Medicine on 10/26/2022, before the trial registration on ClinicalTrials.gov.

The study will be carried out in accordance with the Helsinki Declaration. The inclusion, exclusion, and termination criteria for this trial are as follows:

#### Inclusion criteria

Patients are clinically diagnosed as primary aldosteronism with ARR≥37 (PAC showed as pg/ml, renin showed as μIU/mL) and passed through further P.A. confirmatory tests [13] (PAC-post CCT>110pg/ml, PAC-post SSIT >100pg/ml). PAC: plasma aldosterone concentrationPatients with willingness for AVSAge 18 or above, male or female, with legal capacity

#### Exclusion criteria

Patients with suspected adrenocortical carcinoma or pheochromocytoma.Patients do not accept or with a high risk of adrenal surgery.Patients have been subtyping to glucocorticoid-suppressible hyperaldosteronism or familial hyperaldosteronism type III.Patients were diagnosed with Cushing syndrome or subclinical Cushing syndrome.Patients were treated with glucocorticoids recently.Patients with whole body or venipuncture area infection.Patients with venous access thrombosis.Patients are allergic to iodine.Patients with X-ray contraindications.Patients with coagulation dysfunction.Patients are unable to cooperate and follow up.

#### Termination criteria

Life-threatening events or other serious illnesses occurred during the trial.Patients with incomplete basic information or be erroneously included.Patients who dropped out, did not complete all treatment, or could not complete follow-up visits.

### Interventions

#### Description of the pre-, intra-, and postoperative management

Patient data will be collected in a case report form (CRF) designed by study staff during pre-, intra-, and postoperative courses and in 3 and 6 months after surgery or medicine therapy. All these data will be inputted into an electronic database for storage.

#### Participant enrollment and preoperative preparation

Patients will be initially included or excluded during hospitalization in the endocrinology department based on the patient’s basic information and medical history. The selected patients will be randomly divided into the 15-min supine group (experimental group) or the 2-h group (control group). Before surgery, patients will be informed of the risks, possible complications and expected examination results of AVS surgery, and signed informed consent.

Preoperative examination includes the following: (1) Adrenal enhanced CT: routine CT examination is performed to evaluate whether there are nodules, hyperplasia, and anatomical variation in bilateral adrenal glands; MRI examination was the alternative option for patients with renal insufficiency. (2) Necessary examination for surgery: complete blood count, serum chemistry profile, routine urinalysis, coagulation function, blood group, epidemic disease profile, electrocardiogram; (3) serum potassium, renin, and aldosterone.

Preoperative preparation includes the following: (1) replacing the drugs that may affect the serum renin and aldosterone, especially the mineralocorticoid receptor antagonist (MRAs); (2) keeping serum potassium in the normal range if possible (at least ≥ 3.0 mmol/l); (3) keeping blood pressure within the range of 140/100mmHg.

#### Adrenal vein sampling procedure

On the surgery day, surgeon and nurse will complete the double check, routine medical record, and signature. Patients of the 15-min group will be first sent to the operating room and kept supine before surgery, and femoral vein sheath inserting will be conducted at the end of supine time. During the operation of the 15-min group, the patient of the 2-h group will be sent to the waiting room and kept supine for 2 h. The surgery procedure is the same in both two groups, which were described below.

AVS without corticotropin stimulation was performed by two professional surgeons ([name] and [name]) as previously described [15]. Briefly, a 5-F sheath was placed into the right common femoral vein under the local anesthetic. The left adrenal vein sampling was accomplished in the central adrenal vein by using a 4-F Simon 1 catheter and a 1.8-F microcatheter. The right adrenal vein was carried out by the guidance of coaxial guidewire technique by using a 4-F Simon 1 catheter. Digital subtraction venography helped to confirm the position of the catheters. The regular order of venous sampling was right adrenal vein, IVC, and left adrenal vein. Three milliliters of adrenal venous blood was obtained by intermittent gentle suction. Venous and IVC cortisol levels will be quickly measured by a conventional enhanced chemiluminescence immunoassay (ECLIA; Roche Diagnostics GmbH, Mannheim, Germany).

#### Postoperative management and follow-up

The result of AVS will be interpreted by an experienced doctor. Briefly, in this study, S.I. ≥ 2 indicates successful AVS, and L.I. ≥ 2 indicates unilateral primary aldosteronism. Unilateral P.A. patients will be suggested to accept the unilateral adrenalectomy, and bilateral adrenal hyperplasia patients will be recommended for medication therapy.

Patients will be followed up after unilateral adrenalectomy or optimized anti-hypertensive medicine therapy at 3 months and 6 months with clinical examination. All these data would be recorded in the PASO table, including the blood pressure, type, and dose of antihypertensive drugs, serum potassium, and orthostatic ARR.

